**3.6.4 Data Collection and Measures.**

**3.6.4A Data collection.** Participants will have the option of either receiving an electronic link to complete baseline, 3- and 6-month surveys or they can visit the HEAT clinic and complete the online survey using internet-enabled computer tablets. Survey data will be collected using research and data capture (ReDCap) software. All trial participants will receive the same surveys, with the exception that only the intervention arm will be assessed on implementation process measures (Tables 4). Participants will be given gift card incentives after the survey completion at baseline, 3 and 6 months for a card value of $50, $75 and $75, at those respective time points.

We will also collect data via medical record review. All participants will be asked to complete a medical record release authorization form that will allow us to request the following information from their medical provider(s): HIV testing in past 3 months, last prescription written for HIV PrEP or last ARV prescription written for treatment and last PrEP or HIV medical appointment kept.

**3.6.4B Demographic, Knowledge and Behavioral Factors**. We will assess important baseline characteristics for describing the sample including age, income, gender, education, ethnicity, relationship status, religion, sexual identity, sexual behavior, HIV knowledge, HIV testing readiness, HIV testing history. We will characterize the sample on intersectional stigma by creating a latent variable that is drawn from three scales that measures HIV stigma, same-sex stigma, and gender non-conforming stigma (see Table 4).

**3.6.4C Primary and Secondary Outcomes.** Our primary outcomes will be HIV testing and PrEP use (for HIV-negative or unknown members) or “In HIV care” and “currently on HIV treatment” (for PLHIV) within 6 months of randomization. For HIV-negative MSM we will also record the frequency of HIV testing over the prior 3-months, but we anticipate that few participants will take >1 test in this short period of time. A detailed summary of primary outcome measures is included in Table 3. Our secondary outcomes (see also Table 4) will be number of family-based assets, resilience, number of sexual partners, and relative frequency of CAI. We will also assess sense of community^105^ at all time-points. In our previous research with Black MSM we found that sense of community was associated with increased condom use for anal intercourse (*OR*=1.26, 95%CI 1.05,1.52; p<.05).^14^

**3.6.4D Implementation Outcomes.** We will assess feasibility and acceptability of *OFOV* using a combination of process measures (e.g., intervention completion rate) and validated scales (e.g., peer support evaluation inventory). Implementation outcomes measures are also summarized in Table 4.

**3.6.5 Data Analysis.** The intervention outcomes will be assessed using a rigorous intention-to-treat (ITT) approach where participants are included in the analysis as originally assigned, regardless of whether they actually receive the intervention or usual care.^111^ First, we will compare baseline data to see if randomization resulted in equivalent groups. If we determine non-equivalence, then the non-equivalent variables will be accounted for in the final analyses using a difference in differences analytic technique where randomization is used to minimize any perception of bias in selection of families by investigators. We will determine the proportions of HIV testing at 3- and 6-month of follow-up assessments among family members with 95% confidence intervals (CI). To test the primary study hypotheses that the intervention will increase uptake of HIV testing (for HIV negative members) and attendance at medical care appointment and ARV use (among PLHIV) within six months of randomization, we will use an uncorrected chi-square statistic, followed by effect size calculation with relative risk (RR). As odds ratio (OR) may overestimate RR for common events like in our study, we will use a modified Poisson approach to estimate RR of intervention relative to SOC and CI by using robust error variances.^112^ Additionally, a modified Poisson regression approach will also be used to compute the RR and 95% CI for the binary outcomes (yes/no) – HIV testing, PrEP use, “engaged in HIV care” and “on ARV treatment”. These outcomes can be dependent on the health care facility (HCF) environment, such that participants at the same HCF may be corrected or “clustered”. To account for the potential post-randomization clustering effect in this CRCT, a generalized linear mixed effects model with a logit link function will be fitted, and this model includes both HCF cluster-level and family-level factors. **See Human Subjects section 4.4. for Power Calculations.**

The likelihood of intervention contamination across the study groups could not be excluded, because some participants may not receive the respective interventions to which they are randomized, e.g., some members of the control group may end up in situations in which they receive some level of support from a HBC family in the intervention group. Therefore, we will also perform per-protocol analysis, which includes only those participants who strictly adhered to the protocol and report the results along with the results of the ITT analyses.

| **Table 4. Summary of RCT Phase Measures** | |
| --- | --- |
| **Construct** | **Sample Items and reliability** |
| **HIV Testing** (self-report and medical record verified) | Number of HIV tests in past 3-months |
| **PrEP Use** (self-report and medical record verified) | Is participant currently on antiretrovirals for HIV PrEP? |
| **In HIV Care** (self-report and medical record verified) | Has participant attended HIV medical appointment in past 3-months |
| **On HIV Treatment** (self-report and medical record) | Is participant currently on antiretrovirals for HIV treatment? |
| **Condomless anal intercourse** (past 3 months) | Relative frequency = # times condoms used during anal sex / total # episodes of anal sex |
| **Number of sexual partners** | Total number of sexual partners in the past 3 months |
| **Sense of Community Scale^105^** (8-items) | I feel like I am a member of my house family (α=0.87 - 0.92) |
| **Brief Resilience Scale^106^** (6-items) | I tend to bounce back quickly after hard times? (α=0.80-0.91) |
| **READY Tool** (24-items)^102,103^ | My family expects me to try my best. I ask my family questions to get ideas. (α=0.85) |
| **Asset Inventory (40-items)^21^** | I seek advice and counsel from my parents. My family has clear rules and consequences. |
| **Intersectional Stigma (Latent Variable)** |  |
| **HIV Stigma Scale^107^** | |
| *Enacted subscale (10-items)* | Has a healthcare worker not wanted to touch you because you have HIV? (α=0.92) |
| *Vicarious subscale (10-items)* | How often have you heard stories about someone with HIV being refused care? (α=0.88) |
| *Perceived subscale (10-items)* | In your community, how many people think a person with HIV is disgusting? (α=0.94) |
| *Internalized subscale (10-items)* | How often do you feel guilty about having HIV? (α=0.83) |
| **Same-sex stigma scale** ^108^(10-items) | How often have you lost a place to live for being homosexual? (α=0.75) |
| **Gender Non-Conformity Stigma Scale^109^** (10-items) | How often have you been called names because of your feminine mannerisms? (α=0.88) |
| **Implementation Outcomes** | |
| **Feasibility:** Recruitment yield | % of eligible HBC families who decide to participate |
| **Feasibility:** Peer Support Evaluation Inventory (PSEI)- Satisfaction Subscale (15-item) | I would recommend this type of support to another family  Receiving support from my family member was convenient for me. (0.96) |
| **Acceptability:** Completion rate | Proportion of participants who complete Our Family Our Voices |
| **Acceptability**: PSEI-supportive interactions^110^(15-items) | My family member accepted me for who I was (α=0.95) |
| **Acceptability:** PSEI-Relationship quality^110^ (30-items) | My family members were dependable (α=0.96) |

**3.7 STRENGTHS AND FUTURE DIRECTIONS.** The proposed study will test a novel adaptation of an intervention that integrates HIV risk reduction with family-based asset-building to increase HIV testing and engagement in medical care among HBC family members. The results of the formative research, including the pilot trial, will contribute to the evidence base regarding the development of HIV status-neutral interventions that respond to the diversity and complexities of families that are not themselves segregated by health status. The importance of asset-building to facilitate resilience as a part of the domestic HIV response is recognized as a critical missing component that is welcomed by key national stakeholders in the HBC (see letters of support). Based on findings from the pilot CRCT, we will finalize a protocol for a full CRCT application to conduct a definitive test of the efficacy of *OFOV* to improve HIV testing, PrEP use, care engagement and ARV treatment.

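### The per-protocol analysis is offered as the answer to contamination of controls, but no measure listed in the protocol would identify a contaminated control

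*Protocol*

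**What the plan says.** The main analysis in Protocol 3.6.5 is intention-to-treat: "participants are included in the analysis as originally assigned, regardless of whether they actually receive the intervention or usual care". The same section then says that contamination cannot be ruled out, and its example is that "some members of the control group may end up in situations in which they receive some level of support from a HBC family", meaning one randomised to OFOV. It draws the consequence directly: "we will also perform per-protocol analysis, which includes only those participants who strictly adhered to the protocol". The authors will "report the results along with the results of the ITT analyses".

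On data collection, 3.6.4A gives both arms the same surveys at baseline, 3 and 6 months, with one exception: "only the intervention arm will be assessed on implementation process measures". The one adherence measure in Table 4 is the completion rate, "Proportion of participants who complete Our Family Our Voices". The medical record review in 3.6.4A covers HIV testing, the last PrEP or ARV prescription and the last appointment kept. Under 3.6.1 the control arm is wait-listed on standard of care and receives no group or family programme during follow-up.

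**The concern.** The reason given for the analysis and the data available to it do not match. The stated problem lies in the control arm, while the measures that could define adherence lie in the OFOV arm. Controls have no programme to complete, and nothing listed records whether a control had contact with an OFOV family about the programme or saw its content.

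Two things follow if the analysis is run on the listed measures. Exposed controls stay in, so the dilution that prompted the analysis is untouched. OFOV members who missed sessions or boosters come out, so self-selected completers are compared with an unselected control arm. Willingness to attend may well go with willingness to test, take PrEP or attend care, which are the primary outcomes.

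What is at stake is how the pilot is read. Estimating effect size is a declared aim (3.4.1), and the results feed a full trial application (3.7). A second RR, introduced as the response to contamination and printed beside the ITT result, could be taken for the undiluted effect.

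The gap is one of data collection. A statistical analysis plan can define strict adherence, but it cannot recover exposure data that were never collected.

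**Working it through.** **Can the listed measures flag an exposed control?**

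- Common surveys (Table 4): testing, PrEP, care, treatment, sexual behaviour, sense of community, resilience, READY, asset inventory and stigma scales. The sample items that mention family refer to the participant's own family. None refers to OFOV content or to another family's support.
- Process measures (Table 4): recruitment yield, completion and peer-support scales. 3.6.4A limits process measures to the intervention arm.
- Record review (3.6.4A): testing, prescriptions and appointments only.

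No listed source identifies exposure among controls.

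**Inputs for the illustration**

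- From the protocol (3.4.4A): past 3MV completion 153/174 = 0.879, which reproduces the stated 87.9%; 3-day retention of 68% in the local format and 100% in the retreat format.
- Assumed, because the protocol text at hand gives no such figures: uptake without OFOV p = 0.50; completer minus non-completer gap g; OFOV effect e = 0.15 among completers; a fraction c of controls contaminated, each receiving half the effect. No controls are excluded.

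**No true effect.** With adherence a, completers' uptake is pa = p + g(1 − a). ITT RR = 1.00 and per-protocol RR = pa/p.

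| Adherence a | g = −0.10 | g = 0 | g = +0.10 | g = +0.20 | g = +0.30 |
|---|---|---|---|---|---|
| 68% | 0.94 | 1.00 | 1.06 | 1.13 | 1.19 |
| 87.9% | 0.98 | 1.00 | 1.02 | 1.05 | 1.07 |
| 100% | 1.00 | 1.00 | 1.00 | 1.00 | 1.00 |

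Example: a = 0.68 and g = 0.30 give pa = 0.50 + 0.30 × 0.32 = 0.596, and 0.596/0.50 = 1.19.

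**True effect with contamination.**

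- Control uptake = p + 0.5ce
- ITT RR = [a(pa + e) + (1 − a)(pa − g)] / (p + 0.5ce)
- Per-protocol RR = (pa + e) / (p + 0.5ce)
- Uncontaminated RR among completers = (pa + e)/pa

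At a = 0.879 and g = +0.20, pa = 0.50 + 0.20 × 0.121 = 0.524, and the uncontaminated RR is 0.674/0.524 = 1.29.

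| Controls contaminated | Control uptake | ITT RR | Per-protocol RR | Uncontaminated RR |
|---|---|---|---|---|
| 20% | 0.515 | 1.23 | 1.31 | 1.29 |
| 50% | 0.5375 | 1.18 | 1.25 | 1.29 |

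The per-protocol RR is slightly too high in the first row and too low in the second. At 100% adherence with 20% contamination, ITT and per-protocol are both 0.65/0.515 = 1.26, against 1.30 without contamination: the per-protocol step removes none of the dilution. In every case the contaminated control uptake stays in the denominator.

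**The case against.** A reader might infer that the trial cannot identify contaminated controls at all, that only OFOV members would be dropped, and that the estimate is therefore biased in favour of OFOV. The protocol does not support that much.

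- Table 4 is a summary with sample items, so an unlisted exposure question is possible. What can be said is that no listed measure identifies exposure.
- The per-protocol rule is not confined to one arm, and its evident intent is to exclude exposed controls too. Controls could also be removed for other deviations. That exclusions would fall mainly on OFOV non-completers is an inference from the listed measures.
- Bias towards OFOV requires completers to be more health-seeking. No figure in the protocol shows this; a zero gap gives no bias and a negative gap reverses it. Undetected contamination works against OFOV.
- The 87.9% pools two delivery formats, and OFOV is a retreat. At the 100% retention reported for retreats the selection effect vanishes. That figure, however, is 3-day retention. It does not cover members who decline when asked again before departure (3.6.2C) or who miss any of the four boosters (3.6.3B), should these count as non-adherence.
- The analysis is supplementary to ITT in a pilot with three families per arm, and contamination is also addressed by design, through family randomisation (3.6.1) and video links that cannot be forwarded (3.6.3B).

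These points limit the size and direction of the problem. They do not supply the missing exposure data, and a restricted video link does not prevent the person-to-person support that 3.6.5 itself describes.

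**Conclusion.** The concern holds in a limited form. On the measures listed, the per-protocol analysis would not correct for the contamination that is given as its reason, and it would add one-sided selection.

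With no true effect, the spurious RR is about 1.02 to 1.19 for adherence of 68% to 87.9% and assumed gaps of 10 to 30 points in favour of completers. It is near 1.00 if adherence approaches 100%. These sizes also rest on an assumed 50% uptake without OFOV and on no controls being excluded. When contamination and a true effect are both present, the estimate can fall on either side of the uncontaminated value, so no net direction should be claimed.

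The ITT analysis is unaffected by this point. This is a worthwhile, low-cost improvement to a supplementary analysis, and it has to be made before follow-up data are collected.

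**What to change.** 1. In 3.6.4A and Table 4, add one or two items to the common 3- and 6-month surveys in both arms: contact with an OFOV family about the programme, and viewing of OFOV content.
2. In 3.6.5, commit to reporting contamination by arm, and use these items to define adherence in the control arm.
3. In 3.6.5, state that the per-protocol result is descriptive, is subject to selection, and is not a contamination-corrected effect. Keep ITT as the main analysis.

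A complier-average estimate is not recommended as a substitute. Members who miss the retreat may still be affected through their family, and three families per arm would give an unstable estimate.

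The cost is a slightly longer survey and a few sentences in the protocol. The new items are self-reported, so some exposure will still be missed.

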**3.4.4B. Capacity to engage HBC members in clinical services**. During the same period of 2017 to 2019, HEAT, in collaboration with **The Federation** and **The Coalition (**see Box 1**)**, engaged 57 HBC members living with HIV into HIV primary care and 33 in PrEP medical services. Many of the HBC members entering clinical care at HEAT are referred through or enter care because of HEAT’s HBC engagement. HEAT’s engagement with the HBC extends past intervention groups such as 3MV. HEAT additionally hosts its own HBC events including balls and smaller house-based events such as “house” parties, game night, movie events and others where HIV and STI screening are offered outside the clinic. Through entry into care at HEAT, HBC members have access to HIV 4^th^ generation Ag/Ab testing, HIV viral load testing, screening/testing/treatment for syphilis, gonorrhea and chlamydia, and prescription of ARV and PrEP. This ability to engage HBC members both in a clinical capacity as well as in the community is a key strength of HEAT as a partner in the proposed study.

**3.4.4C. Pilot of 3MV to include HBC members living with HIV.** In 2010, MPI [name] and [name] adapted 3MV for use with HBC youth living with HIV (NYC AIDS Fund, October 2010).
[figure not shown]

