Our working hypotheses are that the *OFOV* intervention will increase uptake of HIV testing and PrEP use (for HIV-negative family members) and linkage to care and treatment engagement (for PLHIV who were not in care at baseline). We will measure frequency of HIV testing at 3- and 6-months post-intervention using a combination of online self-report survey and verification by through clinic medical records. We will seek to obtain medical records releases from participants to obtain data on HIV testing, PrEP prescription, engagement in care and ARV use. Our secondary hypotheses are that *OFOV* will increase the number of family-based assets, resilience and reduce number of sex partners and frequency of CAI for members who are not in mutually monogamous relationship with an HIV-negative or virally suppressed partner. We also measure intersectional stigma and asset-impact indicators at all time points (to characterize these in our sample) ^102,103^ Families in the waitlist SOC control arm have the option to participate in OFOV after 6-month data collection.

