**3.6.2 Procedures**

**3.6.2A Recruitment and Sample****.** We will recruit six HBC families (n=100). See Human Subjects section *4.4. Statistical Design and Power* for sample size and power calculations. We will conduct recruitment using three methods. First, we will disseminate recruitment/marketing materials via **The Federation**, **HLM** and **The Coalition’s** online communication platforms. Potential participating families can contact the study office directly via text message or phone call in response to marketing materials. Second, we will recruit through receipt of referrals of interested families from **The Federation**, **HLM** and **The Coalition’s** programs and outreach activities. Research staff have extensive experience engaging MSM for research and program activities. Third, we will also rely on word-of-mouth as a mechanism through which families become aware of the study and contact us.

**3.6.2B Inclusion/Exclusion Criteria.** Eligibility for the study will be determined primarily at the family-level. At least 12 members of the same HBC family must be willing to participate together, of which at least half the participating members must be Black MSM. Participating family members must reside in the New York City metro area. Black MSM participants must be at least 18 years old. [name], who is a pediatric HIV specialist, believes that the social risk of a confidentiality breach to the biological family is heightened for youth under the legal age of emancipation. Furthermore, we could not justify the risk of enrolling people younger than 18 since our research aim can reasonably be addressed without their inclusion. In addition, Black MSM must also currently self-identify as cisgender or transgender man, report anal sex with another man at least once within the previous six months (note: other HBC family members can identify as any gender).

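### PrEP is analysed as current use in all HIV-negative or unknown members, with conditional baseline adjustment, so the relative risk understates any effect on starting PrEP and keeps moderate chance imbalance

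*Protocol*

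**What the plan says.** - **Hypothesis (3.6.1).** OFOV "will increase uptake of HIV testing and PrEP use (for HIV-negative family members"). For people living with HIV, the matching hypothesis on care is restricted: "for PLHIV who were not in care at baseline". No such restriction is set for PrEP.
- **Outcome and denominator (3.6.4C).** "Our primary outcomes will be HIV testing and PrEP use (for HIV-negative or unknown members").
- **Measure (Table 4).** "Is participant currently on antiretrovirals for HIV PrEP", by self-report with medical record verification. This records status at the time of asking, not starting.
- **Eligibility (3.6.2B).** "Eligibility for the study will be determined primarily at the family-level". The listed criteria do not exclude people already on PrEP.
- **Size (3.6.2A, 3.6.2D).** "We will recruit six HBC families (n=100"), three clusters per arm. Allocation is covariate-constrained, but the covariates are not named.
- **Analysis (3.6.5).** Modified Poisson RR with 95% CI for PrEP use as a yes/no outcome. On baseline differences: "If we determine non-equivalence, then the non-equivalent variables will be accounted for in the final analyses", by difference in differences. No baseline PrEP term is named outside that condition.
- **Prior PrEP use in the community (3.4.4B).** In 2017-2019 the study clinic and its partners "engaged 57 HBC members living with HIV into HIV primary care and 33 in PrEP medical services".

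**The concern.** A member on PrEP before randomisation who stays on it counts as a success in either arm, although OFOV cannot have caused that person to start. Such members add the same amount to both arms' proportions, so the ratio shrinks toward 1 even when the arms are perfectly balanced. With only three families per arm, earlier PrEP use can also differ between arms by chance, and that difference carries through to follow-up.

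The trial exists partly to give a preliminary effect size (3.4.1), and its findings feed the protocol for a full trial (3.7). If the PrEP RR mixes starting with continuing and keeps chance differences in prior use, it is a poor planning figure for an effect on uptake.

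**Working it through.** The protocol gives no PrEP rate, ICC or continuation rate, and it refers power to a Human Subjects section that is not at hand. There is therefore no stated figure to reproduce, and the rates below are assumptions.

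**Group size.** 100/6 = 16.7 members per family. With HIV prevalence of 20% (the upper figure in 3.1), 16.7 × 0.8 ≈ 13 HIV-negative or unknown members per family, or 3 × 13 = 39 per arm.

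**Step 1: dilution with balanced arms.** Let b be the share on PrEP at baseline in both arms. Assume 85% of them continue in both arms, and that initiation among non-users is 30% (OFOV) v 10% (control), an initiation RR of 3.0.

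RR on current use = [0.85b + 0.30(1 − b)] / [0.85b + 0.10(1 − b)]

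| b | OFOV | Control | RR, current use | RR, initiation |
|---|---|---|---|---|
| 10% | 0.355 | 0.175 | 2.03 | 3.0 |
| 20% | 0.410 | 0.250 | 1.64 | 3.0 |
| 30% | 0.465 | 0.325 | 1.43 | 3.0 |
| 40% | 0.520 | 0.400 | 1.30 | 3.0 |

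With balanced arms, adding baseline PrEP status to the Poisson model returns the same RRs. Adjustment does not undo dilution. Only an estimate among baseline non-users does.

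**Step 2: chance gaps in baseline use.** Beta-binomial simulation, 200,000 draws per setting, simple 3 v 3 allocation, 13 members per family, baseline use 20-30%, ICC 0.02-0.10:

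- gap of at least 10 points: 37-56% of draws
- gap of at least 20 points: 6-21% of draws

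**Step 3: how often a baseline test would flag the gap.** Section 3.6.5 names no baseline test. Two candidates at p < 0.05 on the same draws:

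| Test | Gaps ≥10 points flagged | Gaps ≥20 points flagged |
|---|---|---|
| Individual-level uncorrected chi-square | 19-39% | 84-99% |
| Family-level t-test (3 v 3) | 9-12% | 20-39% |

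With the individual-level test, unflagged gaps of 20 points or more occur in about 2% of draws at most.

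**Step 4: what an unflagged gap does.** Take 40 per arm, 90% continuation, and initiation of 10% in control.

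- No true effect, baseline 13/40 (OFOV) v 7/40 (control), chi-square p ≈ 0.12: (13 × 0.9 + 27 × 0.1)/40 = 36% v (7 × 0.9 + 33 × 0.1)/40 = 24%. RR = 1.5.
- True initiation 25% v 10%, baseline 7/40 v 13/40: (7 × 0.9 + 33 × 0.25)/40 = 36.4% v 36.0%. RR = 1.01, against an initiation RR of 2.5.

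**Step 5: noise with no true effect.** Settings of Step 2, 85% continuation, 10% initiation in both arms:

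- New starts clustered by family like baseline use: SD of the arm difference is 11-15 points for current use and 8-11 for initiation, so the variance is 39-42% lower for initiation.
- New starts not clustered: 10-14 points v about 8, or 46-64% lower.

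OFOV is meant to work through family norms (3.3), so the first case is the more plausible.

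**The case against.** **Uptake and current use need not contradict each other.** A reader might infer that the hypothesis and the measure are incompatible. The documents do not support that. The phrase in 3.6.1 can be read as uptake of testing, and separately PrEP use. Section 3.6.5 attaches uptake to testing only, 3.6.1 also speaks of current ARV uptake, and several sections say simply PrEP use. Coverage is a legitimate target, and the boosters could affect continuation. The mismatch is mild. What stands is that the RR on current use is not an effect on starting PrEP.

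**There are safeguards.** A reader might infer that with six families even a large baseline gap would go unnoticed. That holds only if the check is made at family level. An individual-level chi-square, the only test that 3.6.5 names (for the outcome), catches most gaps of 20 points or more, and difference in differences would then follow. Constrained allocation could reduce the gap frequencies in Step 2, which assume simple allocation. However, its covariates are unnamed, and the baseline list in 3.6.4B includes HIV testing history but not PrEP history. Gaps of 10 to 20 points remain mostly uncorrected, and neither safeguard touches dilution.

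**Baseline PrEP use is unknown.** A reader might infer from the 33 people in PrEP services that prior use is common in the trial families. The figure has no denominator, covers one clinic and its partners in 2017-2019, and does not place those people in the enrolled families. It shows only that prior use is possible.

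**Detail may sit in an analysis plan.** Covariate lists and supplementary tables often do, and their absence is not the point. The protocol itself fixes the measure, the denominator and a conditional adjustment rule.

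**Conclusion.** The point holds in moderate form. Current PrEP use among all HIV-negative or unknown members mixes starting with continuing. On the assumed rates, an initiation RR of 3.0 shows as 2.03 to 1.30 when 10-40% are on PrEP at baseline, even with balanced arms. Under simple allocation, gaps of at least 10 points would arise in 37-56% of draws, and an individual-level check would leave most of them uncorrected. The null variance of the arm difference is about 40% lower for initiation if new starts cluster like baseline use. A reader might infer that half or more of the variance is avoidable, but that needs unclustered new starts.

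All sizes rest on assumed baseline use, initiation, continuation and ICC. If few enrolled members are on PrEP at baseline, both problems shrink. For a six-family pilot this is a worthwhile, nearly free correction, not a fatal flaw.

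**What to change.** In section 3.6.5:

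1. Report initiation among HIV-negative or unknown members not on PrEP at baseline, and make this the estimate described as uptake. Report continuation among baseline users separately.
2. For current PrEP use at 6 months, include baseline PrEP status in the model regardless of any baseline comparison. State that this removes imbalance and noise but not dilution.

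Baseline status should already be available, since 3.6.4A has participants complete surveys at baseline, 3 and 6 months; it is worth confirming that the Table 4 PrEP item is in the baseline survey.

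**Cost.** Two or three sentences and no new data. The downsides are one more covariate in a small-sample model and fewer members in the initiation estimate.
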